##### Data Collection Through IDIs

IDIs will be conducted with additional participants from all the target populations through one-to-one discussions and will cover aspects similar to the FGDs. However, these will provide an opportunity to gather deeper insights as the interviewer can probe more, note the changes in respondent’s tone and body language, and also have views that are not influenced by group dynamics or social desirability [62].

##### Data Collection Through SBEs

SBEs will be conducted in small groups of 5 to 6 end-users to delve deeper into the causative factors of decision-making and potential avenues for intention-action gaps by using interdisciplinary concepts from behavioral economics and decision science. SBEs will use the insights generated from the FGDs and IDIs to construct a range of decision scenarios that end-users could face in deciding their preferences for a potential prevention product. SBEs will then use a game-based research technique (Ethnolab) to understand the context, emotions, and decision levers that influence decision-making based on these scenarios. Ethnolab is designed to minimize the impact of biases in decision-making, such as fear of value judgment, social desirability, and expectation of higher self-control in the future, which make respondents claim behaviors that may not play out in real life, thereby giving rise to “say-do” gaps [48]. Ethnolab would allow participants to not only discuss preferred attributes but also make real-time decisions revealing their preferences through multiple test scenarios. One of the critical objectives is to decipher the patterns of preference exhibited by different respondents across divergent contexts. Therefore, Ethnolab will help to identify the following:

Past experiences that have led to decision-making criteria, values, norms, or beliefs that influence health behaviors and product preferencePresent goals around health management, relationship management, and life management and how they influence attribute selectionFactors that could lead to preference reversal.

##### Data Collection Through KIIs

In addition, to better understand the environmental, market, programmatic, and policy contexts at the national, state, and local levels, along with decision-making factors and pathways informing HIV policy, KIIs will be conducted with policy makers and health service providers to understand their perspectives on drivers for the adoption and uptake of health innovations. Efforts will also be directed toward seeking their input on implementation and access issues as well as health systems challenges on non–cold chain versus cold chain product requirements and other parameters related to effective delivery and adoption of biomedical interventions to prevent HIV.

#### Sample Selection

The following sample selection criteria will be followed for the abovementioned methods.

##### End-Users

The inclusion criteria for the various target groups are:

Inclusion criteria for MSM, TGW, PWID, and FSWs in the FGDs and IDIs were as follows: Aged at least 18 years, self-identifies as MSM, TGW, PWID, or FSW, and willing to provide informed consent.Inclusion criteria for AGYW in the FGD and IDIs were as follows: Aged 18 to 24 years and willing to provide informed consent. According to the Joint United Nations Programme on HIV and AIDS definition, AGYW fall into the age group of 15 to 24 years [63]. However, given the ethical considerations with respect to minor adolescent girls (15-17 y) in the Indian context and keeping in mind their relatively lower exposure to HIV prevention services, it was decided that for the purpose of this study, only adolescent girls aged 18 to 19 years and adult young women aged 20 to 24 years will be included. Efforts will be made during data collection and data analysis to ensure that perspectives from participants aged 18 to 19 years and those aged 20 to 24 years are disaggregated to bring out the unique highlights from these populations.For FGDs, diverse typologies and subgroups of MSM (kothis [feminine/primarily receptive role], panthis [masculine and primarily insertive role], double-deckers or versatile, gay, and bisexual men), FSWs (brothel or bar based, street based, internet or social media based, and home based), TGW (gharana based and nongharana and those in sex work and those who are not), PWID (who use different types of injectable drugs), and AGYW across the age group (adolescents aged 18-19 years and young women aged 20-24 years) will be recruited.To explore diverse perspectives, maximum variation purposive sampling [64] will be used to recruit individuals from diverse backgrounds such as engaging in sex work; being from lower and middle class; and being single, living with male or female partners, heterosexually married, and representative of male and female PWID groups.

##### Key Informants

For KIIs, the inclusion criteria will be as follows:

Key informants should be aged >18 years, ≥5 years of experience as a community leader or ≥3 years of working experience with population of interest or as a part of the HIV program, and willing to provide informed consent.Key informants will include information-rich individuals who have worked with key populations or have some experience of working with AGYW or in the field of HIV. These may include health service providers (physicians, counselors, nurses, CBO or NGO representatives, and community leaders) and policy makers (program managers and district or state or national level officials).

#### Sample Size

A total of 30 FGDs (2 FGDs per end-user group per site; for 5 end-user groups across 3 sites) and 45 IDIs (3 IDIs per end-user group per site; for 5 end-user groups across 3 sites) will be conducted in Delhi, Mumbai, and Chennai to investigate factors at individual, interpersonal, and sociostructural levels that facilitate or impede the acceptability of bNAbs among susceptible communities in India.

The SBE will mirror the sampling frame and the broad respondent profiles from the FGDs and IDIs. Keeping in mind that Ethnolab elicits the most useful insights in small and intimate settings, the sample would include 6 participants for each end-user group (distinct and different from the participants in the FGD or IDIs) across each site. Thus, the total sample size would be 90. Each instance of Ethnolab will have 6 respondents, and a total of 20 Ethnolab-based SBEs will be conducted across all 3 sites.

In addition, 5 KIIs will be conducted with health care service providers and policy makers in each region, amounting to a total of 15 KIIs. Thus, the total sample size of the qualitative component of the study is expected to be approximately 300 (FGD: 30×8=240, IDI=45, and KII=15).

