**Methods:**

A multisite study will be conducted in Delhi, Mumbai, and Chennai to capture the differences in perspectives among diverse end-users and key informants across the country. The study will use a multimethods design using focus group discussions, in-depth interviews, simulated behavioral experiments, and key informant interviews. A total of 30 focus group discussions, 45 in-depth interviews, 15 simulated behavioral experiments sessions, and 15 key informant interviews will be conducted across 3 sites.

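### The Sample Size section plans 20 behavioral-experiment sessions of 6 people, but its own sample of 90 and the abstract both give 15

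*Protocol article*

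**What the plan says.** The abstract's Methods paragraph announces "15 simulated behavioral experiments sessions" across the three sites.

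The Sample Size section builds the SBE sample from its design. It ties the SBE to the frame used for the focus groups and interviews: "The SBE will mirror the sampling frame and the broad respondent profiles from the FGDs and IDIs". For the interviews it spells that frame out as "3 IDIs per end-user group per site; for 5 end-user groups across 3 sites". It then sets the number per cell, "the sample would include 6 participants for each end-user group (distinct and different from the participants in the FGD or IDIs) across each site", and concludes: "Thus, the total sample size would be 90". The next sentence reads: "Each instance of Ethnolab will have 6 respondents, and a total of 20 Ethnolab-based SBEs will be conducted across all 3 sites".

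The section Data Collection Through SBEs gives a slightly looser group size: "SBEs will be conducted in small groups of 5 to 6 end-users".

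**The concern.** Two adjacent sentences of the Sample Size section cannot both be true. With 6 people per session, a sample of 90 fixes the number of sessions, and that number is not 20. The abstract gives a different count from the one in the Sample Size section.

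The count matters because the SBE is the component that the Analysis section assigns to preference construction and preference reversal, and its session number is an operational target. A team working to 20 sessions of 6 would recruit 30 people beyond the stated 90, in five sessions with no stated group or site. Those people would come from populations for whom the article itself acknowledges confidentiality and social risks. A team that kept to 90 people but ran 20 sessions would run games smaller than planned. At the end, 15 completed sessions could be read as full completion or as 75% of plan (15/20).

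**Working it through.** This is a direct count; no power formula applies.

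**Inputs**

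- End-user groups: 5; sites: 3; hence 5 × 3 = 15 group-by-site cells (Sample Size)
- SBE participants per cell: 6 (Sample Size)
- Respondents per session: 6 (Sample Size); 5 to 6 (Data Collection Through SBEs)
- Stated SBE sample: 90 (Sample Size)
- Stated sessions: 20 (Sample Size); 15 (Abstract, Methods)

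**Step 1. Reproduce the stated sample.** Participants = groups × sites × participants per cell = 5 × 3 × 6 = 90. This matches.

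**Step 2. Derive the sessions.** Sessions = participants / respondents per session = 90 / 6 = 15, one per cell. This matches the abstract and not the stated 20. The excess is 20 − 15 = 5 sessions: 5/15 = 33% above 15, or 5/20 = 25% of the stated 20.

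**Step 3. Work back from 20 sessions.**

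| Respondents per session | Sessions needed for 90 people | People in 20 sessions | People in 15 sessions |
|---|---|---|---|
| 6 | 15 | 120 | 90 |
| 5 | 18 | 100 | 75 |

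Even at the bottom of the range, 90 people fill 18 sessions, not 20. Ninety people over 20 sessions is 90/20 = 4.5 per session, below both 6 and the 5-to-6 range.

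**Step 4. Look for a layout that gives 20.** Over cells, 20/15 = 1.33; over sites, 20/3 = 6.67. Over groups, 20/5 = 4, but 4 sessions per group cannot be split evenly over 3 sites. No even layout across sites or cells produces 20. Two sessions in every cell would give 30.

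**Step 5. Look for an explanation elsewhere.** Data Collection Process for SBE describes one three-part session of at most 2 hours and mentions no pilot or repeat session. The overall total of about 300 in Sample Size is 240 + 45 + 15 for focus groups, interviews and key informants. It leaves the SBE out, so it does not decide between 15 and 20.

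**The case against.** The strongest reply accepts the contradiction and disputes its weight. The participant target of 90 is internally consistent and agrees with the abstract, so a careful reader can see that 20 is the outlier. The rule of 6 people per group per site, at 6 per session, already implies one session per cell. One partner, working with the others, is responsible for the SBE sessions at all sites, so the sites would not each interpret the number alone. Because the study is qualitative and purposively sampled, no estimate or error rate depends on the count. Preferences are also explored in 30 focus groups and 45 interviews.

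Much of this is fair. It supports 15 as the better reading, and it means that the harm in practice is possible rather than certain. It does not remove the error: the section still states a session count that contradicts its own sample, and nothing in the article says which was intended.

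The group-size mismatch is a minor matter. The article also gives focus groups as 7 to 8 people and then sizes them at 8 (30 × 8 = 240), so using the top of a range looks like its convention. The uneven division of 20 over sites and cells adds little once 90 against 120 is established. It mainly shows that no obvious allocation explains the figure.

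**Conclusion.** The concern holds. The 20 sessions in the Sample Size section are inconsistent with the 6-per-cell design, with the total of 90 and with the abstract, all of which give 15. The overstatement is 5 sessions, or 33% taking 15 as the base. In people, it is 120 against 90 at 6 per session, or 100 if groups of 5 were used.

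The conclusion assumes that the SBE uses the same 5 groups and 3 sites as the focus groups and interviews, which the article says and which its own total of 90 confirms. It also assumes that each participant attends one session, since no repeat attendance is described. The article does not declare which count was intended; 15 is the better supported. The effect is on recruitment, workload and the ability to judge completion, not on any statistical error rate.

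**What to change.** In the Sample Size section, replace 20 with 15 and add that this is one session per end-user group per site. State the group size consistently in both places: either 6, or 5 to 6 with the total given as 75 to 90 (15 × 5 to 15 × 6). This costs one number and one aligned phrase, with no new participants.

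If 20 sessions were truly meant, restate the SBE sample as 120, change the abstract from 15 to 20, revise the per-cell rule of 6, and say which groups and sites receive the five extra sessions and why. That route adds 30 participants (120 − 90) and the corresponding session work.

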#### Implementing Partners

The implementing partners for the study are YR Gaitonde Centre for AIDS Research and Education (YRGCARE), Centre for Sexuality and Health Research and Policy (C-SHaRP), and The Humsafar Trust (HST), who will be responsible for conducting the FGDs, IDIs, and KIIs. The designing of the Ethnolab game–based data collection method will be done by Final Mile and IAVI. Final Mile, in working with other study partners (YRGCARE, C-SHaRP, and HST), will be responsible for the implementation and conduct of the SBE sessions across all study sites.

### Data Collection

#### Overview

Data from FGDs, IDIs, and KIIs will be collected using semistructured interview topic guides. Trained research staff will conduct the FGDs, IDIs, and KIIs. The research staff will receive additional training specific to the content of this study and research ethics. SBEs will be conducted by partner consultants and will also include a round of initial meetings with the other study clinical research center partners to ensure alignment with the findings from the FGDs and IDIs.

#### Lines of Enquiry for FGDs and IDIs

For the FGDs and IDIs among end-users, the following broad areas will be covered in the lines of inquiry:

Preference elicitation questions: Under this process, the group will be asked about individual product attributes and their preference for different features under that attribute. The process will aim to understand which attributes matter most to the populations and the preferences for different subgroups under that population to gain an overall community-level perspective. Efforts will also be made to understand the reasons for these preferred options. This section would also cover the individual, interpersonal, and social concerns that might drive end-user decision-making.Relative desirability of predetermined product profiles (attribute bundles): As a next step, participants within each focus group will be presented with 4 product profiles comprising 5 to 6 attributes in different combinations (bundles) through a mixture of visual methods and information, education, and communication tools. These are modeled after various HIV prevention products, including the current bNAb product under investigation. Participants will be requested to choose their “most/least preferred” profiles, rank the remaining 2, and explain the reasons behind their choice. In addition to enabling a deeper understanding of preferences and trade-offs, this would also aid in understanding the most critical attributes informing decision-making on product use among prospective end-users.

The topic guide will be translated into native languages (Hindi, Tamil, Telugu, or Marathi), back-translated into English, and then revised in the original language. All discussions will be audio-recorded, transcribed, and translated. They will be deidentified before proceeding for further data analysis. Each FGD and each IDI will span over 60 to 90 minutes.

#### Data Collection Process for SBE

The SBE sessions will consist of three parts:

*Ethnolab Conundrum game*: The Conundrum game will expose participants to multiple scenarios, each ending with a decision conundrum having different possible outcomes. Each scenario will simulate the real-world context of participants by representing a protagonist of the same age, gender, and socioeconomic level in a relevant health-related situation. The scenarios will be constructed using preliminary insights generated from the FGDs and IDIs, with decision points informed by heuristics and behavior science principles. The research is gamified: participants will be asked to respond quickly in real time and choose the option they think will coincide with most respondents in the group and will win points if it does. The game will thus generate responses representative of mental models, emotions, and biases rather than deliberate and rational analysis [48]. Preference reversal will be tested through tweaks in the context simulation and the framing of attributes.*Ideal product profile exercise*: The participants will go through a series of prompts to design the ideal prevention product suited to their needs. This activity will be an adapted version of the product profile ranking exercise used in the first round of qualitative research. It will be designed to give participants an expanded choice set to clearly articulate their trade-offs and allow for tracing certain preference reversal patterns. This will enable an overall high engagement and easy and detailed discussion on product attributes.*Group conversations*: Once the games are over, participants will be split into multiple groups of dyads and triads for group conversations (where scenarios and reactions are still fresh in their minds) regarding the experience, decisions, and preferences in the game [50]. The conversations on the scenarios provide opportunities for improved contextualization of the responses, understanding emotions and other causative factors behind preferences, and tracing decision pathways.

The data generated from the games, along with the ensuing conversations, will help elicit behavioral insights and identify intrinsic drivers and extrinsic factors influencing the preferences and decisions of prospective end-users. The Ethnolab play will last for approximately 60 minutes, and the subsequent group discussions will last for 45 minutes. The overall activity will not exceed 2 hours. The session will involve engaging games to maintain a playful environment, and adequate breaks will also be incorporated to ensure that the time of engagement does not become burdensome for the participants.

#### Lines of Enquiry for KIIs

Semistructured interview guides will consist of 10 to 12 open-ended questions and scripted probes. The interview guides will be translated into native languages (Hindi, Tamil, or Marathi), back-translated into English, and then revised in the original language. Key informants for each study population will be asked questions for the need perception of a prevention product, preference and importance of product attributes, social and cultural acceptability, risk compensation, health systems readiness, and alignment with the policy environment in India. Each KII will be conducted for approximately 90 minutes.

### Data Analysis and Validation

#### Analysis

The qualitative approach will use triangulation to strengthen and ensure the accuracy of data [65]. According to Denzin and Lincoln [66], triangulation is a process in which several methods are used in the study and might be used in four basic ways: (1) data triangulation, (2) methods triangulation, (3) theory triangulation, and (4) researcher triangulation. In this study, data triangulation, methods triangulation, and researcher triangulation will be used. All transcripts will be redacted (to remove any personally identifying information that might inadvertently have been recorded) and uploaded into NVivo (Lumivero) or Dedoose (University of California). First, a line-by-line review of the transcripts will be performed, and first-level codes will be identified to create a common a priori codebook (based on the adapted conceptual or theoretical framework and topic guides). All codes will be then entered and tagged to associated chunks of text. Texts corresponding to each of the first-level codes will be coded by at least 2 independent analysts and reviewed by senior investigators. Explanatory or theoretical or etic (researcher generated) codes will be arrived at using a constant comparative method [67].

The SBE results will be analyzed using the cognitive and emotional appraisal framework [68] as a base. Appraisal theories are componential theories that view an emotional episode as involving changes in a number of organismic subsystems and components. The components could include an appraisal, a motivational, a somatic, and a motor component. The framework will be used to generate the codebook and will then feed into the 4 major categories of context, emotions, mental models, and decision levers. This will be done along with the ranking of preferences drawn from the experiential game data. The SBEs will be analyzed to gain an in-depth understanding of (1) preference construction and (2) preference reversal.

#### Validation

Data source triangulation and researcher triangulation will enhance the reliability and trustworthiness of the findings [69]. Thus, study implementation and data analysis will also incorporate researcher reflexivity and researcher triangulation by maintaining “quicknotes” (a brief summary of every interview or focus group by the interviewers or moderators that will be shared with the analysts and investigators for feedback), writing memos, and engaging in peer debriefing to maintain ongoing awareness of our social location and how it may influence the research process and interpretation. A maximum of 2 interviewers or moderators will be used for every population of interest to ensure that there is minimum bias in the way questions are asked or follow-up probes are used.

#### Data Security for Storage and Transmission

Names or other personal identifiers will not be collected from the participants. Only the investigators and key research staff at the participating research sites will have access to the transcripts or translated text and digital recordings. As soon as an interview is completed, the audio file will be transferred from the digital recorder to password-protected computers. Subsequently, the file will be deleted from the digital recorder. The transcriptionist and translator will sign a confidentiality pledge stating that they will not reveal any information from the interviews to anyone else. The digital copies of transcripts and translated text will also be stored on password-protected computers.

Only this study’s research staff at the participating research site will have access to the audio files, transcripts, and translated text. All digital recordings will be redacted, and any personal identifying information will be removed. Digital recordings will be deleted after 1 year (the 1-year delay is to ensure that there are no gaps in the transcripts). Redacted transcripts will be maintained for 2 years and then destroyed. Informed consent forms will be separately stored and will include signs, initials, or “X” marks rather than names. Unique identification codes will be assigned to all individual records, including digital recordings and transcripts. Hard copies of the data and related documents will be stored in a secure location in locked cabinets in the offices of study and will be accessed only by the research staff.

